## Sample size

The sample size calculation for the primary outcome (change in MOXFQ walking/standing domain by 52 weeks post-op) was performed using Stata/IC version 12.1 [15]. It was based on achieving 90% power to detect the minimal clinically important difference (MCID) in the primary outcome at the 5% level of significance, accounting for expected loss to follow-up. The trial is multi-centre and the outcome plausibly varies by surgeon, so the sample size was adjusted to account for clustering; the intraclass correlation coefficient (ICC) was estimated based on previous studies, and the initially computed sample size was inflated by a factor f = 1 + (m − 1) ∗ ICC [16].

The sample size calculation was partly based on the study by Dawson et al. [9] which defined the MCID in the MOXFQ when evaluating outcomes following surgery for hallux valgus. They defined it as the mean change in MOXFQ of those patients who reported feeling at least “slightly better”, and found it to be 16, 12, and 24, respectively, for the standing/walking, pain, and social interaction domains of the MOXFQ. For this trial we determined it was important to detect a difference of 12 in the change from baseline in MOXFQ standing/walking domain between the two treatment arms; a conservative choice given the threshold for a MCID in the standing/walking domain found in the Dawson et al. study was 16. The standard deviation of the walking/standing domain of the MOXFQ was estimated as 27 [11], and loss to follow-up was estimated as 10% (attrition in similar RCTs has been 5–7% [17]).

Based on these quantities, the required sample size was estimated as 118 patients per arm. Assuming an average cluster size (m) of 14 (patients per surgeon) and an ICC of 0.03 (estimated from the median of ten previous surgical studies reporting patient-reported disease-specific measures 12 months post-surgery [18]), an inflation factor of f = 1.39 was estimated, leading to a final required sample size of 164 per arm or 328 patients total.

The assumptions of ICC = 0.03 and equal numbers of patients per surgeon in the sample size calculation [19] were reviewed by the trial statistician prior to the end of recruitment using the available data. The review indicated lower ICC and also some variability in numbers of patients per surgeon compared to the original assumptions (ICC < 0.01; average cluster size = 15, standard deviation = 9.6), resulting in increased power.

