### Significance levels of tests and confidence intervals

All statistical tests will use a two-sided *p* value of 0.05, unless otherwise specified. There will be no formal adjustment of *p* values for any interim analyses performed. Two-sided 95% confidence intervals will be presented for all estimates.

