#### Sensitivity analyses

The robustness of the results to assumptions made about missing data in the primary outcome will be assessed. The primary analysis is only valid if the distribution of the 52-week MOXFQ scores are not different between the responses which are observed and those which are unobserved (conditional on all baseline response and covariates, treatment, and 26-week post-op response), i.e. if these data are missing at random.

Firstly, characteristics of patients missing a 52-week response will be investigated using logistic regression, with an indicator for missing data modelled on baseline covariates and the data items collected at 26 weeks post-op. Results from the model will provide contextual information regarding the missing data and, together with qualitative information gathered from the site teams, will be used to explore potential mechanisms for missing data.

Secondly, if more than 10% of patients operated on are missing 52-week MOXFQ scores (the attrition assumed in the original sample size calculation), a sensitivity analysis will be done to explore the impact of the primary outcome data being missing not at random (MNAR). A pattern mixture modelling approach will be adopted for the analysis [25]. It will explore how different the unobserved responses would have to be from the observed responses for inferences from the primary analysis to change; specifically, how extreme the departure from MAR would have to be for the *p* value to change from *p* < 0.05 to *p* ≥ 0.05 (or *p* ≥ 0.05 to *p* < 0.05).

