In brief, multiple imputation will be used to produce and analyse datasets with 52-week MOXFQ imputed on the assumption that it is missing randomly conditional on the other recorded variables. The number of imputation datasets created, n, will be chosen to give a power reduction of < 1% compared to using *n* = 100 [26]. Then, the imputed 52-week MOXFQ scores will each have a number Ø added to them, and the multiple imputation primary analysis model will be run (with estimates combined using Rubin’s rules [27]). The value of Ø which causes the *p* value for the 52-week treatment effect estimate to cross the 0.05 boundary will be identified and reported. This number is interpretable as how different MOXFQ would have to be from expected amongst the patients who did not attend at 52 weeks for the analysis conclusions to change. The possibility that data are MNAR in one treatment group only will also be explored: only imputations in the TAR group will be edited (missing data for the arthrodesis group remain imputed under MAR) and the Ø which causes the 52-week treatment effect estimate to cross the 0.05 boundary will be identified. Subsequently, only imputations for the arthrodesis group will be modified as described above. Alongside information on the characteristics of the patients missing 52-week MOXFQ scores, these analyses will be used to consider whether missing outcome data may compromise conclusions from the primary analysis.

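### The tipping-point run that adds one Ø to both arms nearly cancels from the treatment difference when missingness is similar, so its crossing value should not be read as robustness; departures differing between arms should be examined jointly

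*SAP article*

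**What the plan says.** The SAP article, section Sensitivity analyses, plans a pattern-mixture tipping-point analysis if more than 10% of operated patients lack a 52-week MOXFQ score. Its aim is to find "how extreme the departure from MAR would have to be for the" p value to move across 0.05 in either direction.

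Scores are imputed under MAR, and three runs follow:

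- **Common shift.** "the imputed 52-week MOXFQ scores will each have a number Ø added to them". No arm is named, so the same Ø goes to both. The article then comments: "This number is interpretable as how different MOXFQ would have to be from expected amongst the patients who did not attend at 52 weeks". The rest of that sentence ties this figure to a reversal of the trial's finding.
- **TAR-only shift.** "The possibility that data are MNAR in one treatment group only will also be explored". TAR imputations are shifted and arthrodesis imputations stay under MAR.
- **Arthrodesis-only shift.** The same with the arms exchanged.

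The three runs, with the characteristics of patients lacking a 52-week score, feed one judgement on whether missing data threaten the primary conclusion. None is ranked above the others. The section does not say what is reported if no Ø makes p cross 0.05.

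**The concern.** A treatment comparison is threatened mainly when the unobserved scores depart from MAR differently in the two arms. A shift of the same size in both arms largely subtracts out. If the arms lose similar fractions, the common Ø tests chiefly how much extra variance is needed to lose significance, not how much bias would reverse the finding.

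The explanatory sentence is nevertheless attached to that run and carries no restriction to equal departures. A reader who sees a common Ø of 70 points, or sees that none exists, may conclude that the result is safe. A departure of a few points differing between arms could still overturn it.

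This matters here because patients, surgeons and assessors are unblinded and the outcome is self-reported, so reasons for non-attendance may differ by arm. The two arms could even depart in opposite directions, and none of the three runs looks at that.

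**Working it through.** **Inputs from the SAP article.** 303 randomised 1:1, about 151 per arm (Background; Randomisation and blinding). "The standard deviation of the walking/standing domain of the MOXFQ was estimated as 27" (Sample size). Two-sided 0.05 (Significance levels). Scores run from 0 to 100, higher is worse (Calculation of outcome scores). The trigger is more than 10% missing (Sensitivity analyses).

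**Assumptions.** Missing fractions by arm and observed differences are not given, so ranges are shown; 10% per arm sits at the edge of the trigger. A normal approximation is used, with no gain from baseline adjustment, no use of the 26-week scores and no surgeon effect.

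**Reproducing the plan's own figure.** The article gives no figure for the tipping-point analysis. Its sample size, which uses the same SD, does reproduce. For a difference of 12 and 90% power, n = 2 × [27 × (1.960 + 1.282)/12]² = 106.4 per arm. Then 106.4/0.9 = 118.2, against 118 stated. The design effect is 1 + 13 × 0.03 = 1.39, and 118 × 1.39 = 164.0, against 164 stated.

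**Formulas.** Let d be the observed difference (TAR minus arthrodesis; negative favours TAR), f the missing fraction and Ø the shift in each arm.

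- Shifted difference = d + f_T·Ø_T − f_A·Ø_A
- Variance per arm = [27²/(1 − f) + f(1 − f)·Ø²]/151

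With a common Ø the shift in the difference is Ø·(f_T − f_A), which is zero when the fractions are equal.

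**Worked case: d = −8, 10% missing per arm.** The unshifted SE is √(2 × 810/151) = 3.28 (p = 0.015).

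- Common Ø = 70.6: the difference stays at −8. Variance per arm = (810 + 0.09 × 70.6²)/151 = 8.34, SE = 4.08, and 1.96 × 4.08 = 8.00. The run tips only because the SE has grown.
- TAR only, Ø = 15.4: difference = −8 + 1.54 = −6.46; SE = 3.30; 1.96 × 3.30 = 6.46.
- Opposite signs, Ø_T = +7.8 and Ø_A = −7.8: difference = −8 + 0.78 + 0.78 = −6.44; SE = 3.29; 1.96 × 3.286 = 6.44.

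**Non-significant results with equal fractions.** The common shift leaves d unchanged and can only enlarge the SE, so p can only rise. No common Ø can move p from above to below 0.05. The search up to ±300 agrees.

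**Tipping values, equal missingness (size of Ø in points).**

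| Missing per arm | d | Common | One arm | Opposite signs |
|---|---|---|---|---|
| 10% | −12 | 150 | 51 | 27 |
| 10% | −8 | 71 | 15.4 | 7.8 |
| 10% | −7 | 41 | 5.8 | 2.9 |
| 10% | −6 | none | 4.3 | 2.2 |
| 10% | −5 | none | 14.6 | 7.2 |
| 10% | −2 | none | 48 | 23 |
| 15% | −8 | 56 | 9.2 | 4.7 |

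A common Ø of 150 exceeds the whole width of the scale.

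**Tipping values, unequal missingness (size of Ø in points).**

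| Missing TAR / arthrodesis | d | Common | TAR only | Arthrodesis only |
|---|---|---|---|---|
| 12% / 8% | −8 | 31 | 12.9 | 19.1 |
| 12% / 8% | −6 | 11.8 | 3.6 | 5.4 |
| 15% / 5% | −8 | 15.0 | 10.3 | 29.8 |
| 15% / 5% | −6 | 4.4 | 2.9 | 8.8 |

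Once the fractions differ clearly, the common Ø tips at moderate values. At 15%/5% it is smaller than the arthrodesis-only value.

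**The case against.** The strongest reply is that the section already contains the remedy. The TAR-only and arthrodesis-only runs do not cancel, their tipping values are to be identified too, and the closing judgement rests on all the analyses together. The explanatory sentence can be defended as literally true of a departure shared by all non-attenders. The analysis is also conditional: the plan expects up to 10% missing and cites 5–7% in similar trials, so it may never run. Finally, the shift is additive in the two arms, so a careful reader could work out opposite-signed cases roughly from the one-arm results.

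Much of this stands. A reader might infer that the common-Ø run is the lead analysis, or that the missing-data assessment will come out robust almost whatever the data. The document supports neither. The common run is only described first, two discriminating runs follow it, and the unequal-missingness figures show that the common Ø itself can tip at plausible values.

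Two things remain. The one-arm runs do not correct the unqualified reading given to the common Ø, and nothing says which result governs when the runs disagree, as they will when missingness is similar. Leaving readers to derive the joint departures is also weaker than reporting them from imputations already in hand.

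**Conclusion.** The point holds in a limited form. With similar missing fractions, the common Ø is very large, or absent after a non-significant primary result with equal fractions. It is then not evidence of robustness to departures that differ between arms. In the 10%-per-arm cases that tip (d = −12, −8, −7), it exceeds the one-arm value about three- to sevenfold: 150/51 = 2.9, 71/15.4 = 4.6, 41/5.8 = 7.1. Equal and opposite departures, which the plan does not examine, tip at about half the one-arm value.

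The cancellation and the half-value relation follow from the algebra. The point values rest on SD 27, 151 per arm, the assumed missing fractions and differences, and the simplified variance; the planned mixed model will give somewhat different numbers. The primary analysis is unaffected. This is an inexpensive improvement to a conditional sensitivity analysis.

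**What to change.** In the section Sensitivity analyses:

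1. State that the arm-specific shifts carry the interpretation.
2. Extend them to a two-way grid of Ø_TAR and Ø_arthrodesis that includes opposite signs, limited to values that keep imputed means within 0–100.
3. Report the 52-week difference and its 95% CI over the grid, marking where p crosses 0.05. The common shift is then the diagonal of that grid.
4. Qualify the explanatory sentence: a common shift moves the estimate only through the difference in missing fractions, and a large or non-existent common Ø is not in itself evidence of robustness.

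The cost is a paragraph of text and a loop over imputations already planned. The downsides are a table or contour plot in place of single numbers, and robustness that may look less favourable.

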## Discussion

This update contains the pre-specified statistical analysis plan for the TARVA trial, written to conform with the Journal of the American Medical Association Guidelines for the Content of Statistical Analysis Plans in Clinical Trials [28]. By publishing the statistical analysis plan we aim to increase the transparency of the data analysis. The TARVA trial will provide comprehensive and precise information on the relative effectiveness of TAR versus ankle arthrodesis.

## Data Availability

The protocol has previously been published [6]. Following completion of the trial analysis the results will be published, and additional available data can be obtained by contacting the chief investigator ([name]). The study team retain exclusive use until publication of major outputs has been completed.

## Abbreviations

AE: Adverse event
AP: Anteroposterior
CT: Computed tomography
EQ-5D: EuroQol five-dimension quality-of-life instrument
FAAM: The Foot and Ankle Ability Measure
FAAM-ADL: The Foot and Ankle Ability Measure Activities of Daily Living subscale
FAAM-Sport: The Foot and Ankle Ability Measure Sport subscale
ICC: Intra-class correlation coefficient
ITT: Intention-to-treat; includes all observed data from randomised patients in accordance with their randomised procedure, regardless of whether surgery actually occurred
m: Average cluster size (patients per surgeon)
MAR: Missing-at-random
MCID: Minimal clinically important difference
MI: Multiple imputation
MNAR: Missing-not-at-random
MOXFQ: The Manchester-Oxford Foot Questionnaire
MRI: Magnetic resonance imaging
OA: Osteoarthritis
PIS: Patient information sheet
QoL: Quality of life
ROM: Range of motion
SAE: Serious adverse event
TAR: Total ankle replacement
TARVA: Total Ankle Replacement Versus Arthrodesis trial
T-score: A measurement of bone density expressed in standard deviation units from that of a healthy young adult
UCL CCTU: UCL Comprehensive Clinical Trials Unit
VAS: Visual analogue scale
